**Aim III: To investigate the role of M. pneumoniae genotype on virulence**

*Approach*

See aim I

*Clinical samples*

See aim I

*Clinical data*

See aim II.

*Detection of M. pneumoniae*

See aim I

*Genotyping of the M. pneumoniae P1 gene*:

To type all isolated M. pneumoniae strains, the complete P1 gene of each strain will be amplified by PCR and sequenced. For each strain, at least two independently generated PCR fragments will be sequenced in order to check for potential PCR artefacts. The obtained sequences will be compared to each other and to sequences deposited in the GenBank database (http://www.ncbi.nlm.nih.gov/entrez/query.fcgi?db=Nucleotide&itool=toolbar). Based on the different sequences of the P1 gene, an M. pneumoniae strain classification scheme will be determined and a typing method will be designed. Specific genotypes will be compared to patient data, in order to relate genotype to bacterial virulence.

# Collaboration: influenza research

Concurrently to our study an influenza trial is being conducted in the Erasmus MC-Sophia. Due to the amount of similar research goals and methods, both studies are aiming to obtain the same patient population and same samples. Close collaboration between the research teams enables patients to be less burdened by our studies: parents only need to read one patient information leaflet instead of two separate ones. Moreover, blood sampling is conjugated: blood sampling will be performed on one occasion and after sampling, the blood is split and divided between the researchers. The only difference when participating in both the influenza study and the mycoplasma study is the quantity of the sample. Instead of the 0,5 ml blood which is required for the mycoplama study; 3 to 5 ml blood is wanted for the influenza study. Parents and children need to give their explicit consent before entering both studies: it is stated in the consent form.

#

# STUDY POPULATION

## Population (base)

Age: 0-16 years

Group A: 500 children visiting the Emergency Department/HAP because of upper or lower respiratory tract infection, from which: 400 children <5 years and 100 children ≥ 5 years.

Group B: 500 healthy controls; recruited from children attending the outpatient clinic in preparation of their surgery. Again: 400 children <5 years and 100 children ≥ 5 years.

## Inclusion criteria

Group A

- Age: 3 months and ≤ 16 years
- Clinical signs and symptoms of community-acquired upper or lower respiratory tract infection (i.e. cough, rhinitis, sore throat, wheezing and fever).
- Written informed consent

Group B (control group)

- Age: 3 months and ≤ 16 years
- Written informed consent
- Healthy controls: absence for 1 week of clinical signs and symptoms of community-acquired upper or lower respiratory tract infection (i.e. cough, rhinitis, sore throat, wheezing and fever)

## Exclusion criteria

Group A

- Age: ≤ 3 months and  16 years
- use of antibiotics less than 48 hours preceding enrolment
- use of azithromycin within 1 week preceding enrolment.
- Severe concomitant disease (chronic lung disease, neoplasia, liver or kidney disease, immunodeficiency, cardiovascular disease, psychomotor impairment, nosocomial infection).
- No written informed consent

Group B (control group)

- Age: ≤ 3 months and  16 years
- Clinical signs and symptoms of community-acquired upper or lower respiratory tract infection (i.e. cough, rhinitis, sore throat, wheezing, and/or fever).
- use of antibiotics less than 48 hours preceding enrolment
- use of azithromycin within 1 week preceding enrolment.
- Severe concomitant disease (chronic lung disease, neoplasia, liver or kidney disease, immunodeficiency, cardiovascular disease, psychomotor impairment, nosocomial infection).
- No written informed consent

## Sample size calculation

For estimated group sizes in 2 years of 500 in group A and 500 in group B small differences in mean quantitative result of PCR will be demonstrable (α = 0.05, power ≥ 90%) if the effect-size (difference of mean/standard deviation) is 0.20 or larger, which can be considered as a small difference. Group A we aim to include pre-calculated numbers according to age (400 children, < 5 years, versus 100 children, > 5 years). Because of a high prevalence viral RTI below 5 years of age, it is necessary to include more children with RTI in this group, to find a reasonable number of M. pneumoniae infections. Assuming up to 10% M. pneumoniae infections below 5 years of age we will be able to detect a 12% difference using these numbers in these subgroups (< 5 years versus >5 years). For comparison we aim to include the same numbers in group B (healthy children).

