# STATISTICAL ANALYSIS

Research questions and analysis

Question 1 (objective 1): does asymptomatic carrier state with M. pneumoniae exist (see question 3, we expect to find > 10%, using quantitative PCR) (10), and if so, can asymptomatic carrier state be differentiated from infection using quantitative PCR?

Analysis: in children with respiratory tract infections caused by M. pneumoniae (as defined by positive standard PCR, positive serology, and or positive culture, group A), results from the quantitative PCR (results in copies/ml) will be compared with the results from the quantitative PCR in asymptomatic children (healthy asymptomatic children with positive results from either standard conventional PCR or culture, group B) using the Mann-Whitney U test. A PCR value, which can differentiate asymptomatic carrier state from infection (threshold), will be determined using Receiver Operating Characteristic (ROC) curves. This value should have a high sensitivity and acceptable specificity.

Question 2 (objective 1): what is the sensitivity and specificity of this quantitative PCR?

Analysis: sensitivity and specificity will be determined using Receiver Operating Characteristic (ROC) curves. In addition we will investigate the sensitivity and specificity according to whether the quantitative PCR results in a positive or negative result (lowest possible detecting range is 10 copies).

Question 3 (objective 1): what is the prevalence of asymptomatic carrier state?

Analysis: prevalence of asymptomatic carrier state (a positive result with quantitative PCR) will be calculated in group A (children with a positive quantitative PCR result and RTI not caused by M. pneumoniae) and B (healthy asymptomatic children with a positive PCR result). We expect to find >10% in group B (10).

Question 4 (objective 2): does M. pneumoniae infection occur more often in children older than 5 years?

Analysis: children in group A with a RTI caused by M. pneumoniae will be divided in two groups, according to age (< 5 years and ≥ 5 years) and compared to each other, with respect to the prevalence using 2-test.

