## *Sample size calculation*

This study will be merely descriptive. Currently, about 10% of the enrolled children are tested positive by PCR for *M. pneumoniae*. This ancillary study will commence halfway during the original study, so we expect in total an additional 50 children will be tested positive by PCR and will therefore be eligible for this study.

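### The stated 90% power for an effect size of 0.20 is based on all 500 children per group, but the load comparison in Question 1 uses only M. pneumoniae-positive children, roughly a tenth of them

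*Protocol*

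**What the plan says.** Protocol section 4.4 (Sample size calculation) opens with "For estimated group sizes in 2 years of 500 in group A and 500 in group B". It goes on to say that "small differences in mean quantitative result of PCR will be demonstrable (α = 0.05, power ≥ 90%) if the effect-size", given as "difference of mean/standard deviation) is 0.20 or larger", and it calls this a small difference.

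Section 9, Question 1, defines the comparison of quantitative PCR results between the groups. One side is the set of results "in children with respiratory tract infections caused by M. pneumoniae (as defined by positive standard PCR, positive serology, and or positive culture, group A"). The other is "healthy asymptomatic children with positive results from either standard conventional PCR or culture, group B". The two sets are compared "using the Mann-Whitney U test", and a ROC curve is used to find a threshold.

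On how many children will be positive:

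- Section 4.4 assumes up to 10% M. pneumoniae infections below 5 years of age.
- Section 9 (Questions 1 and 3) expects more than 10% carriage in group B.
- Section 12.1.4 expects 10% positives in each group.
- The sample size paragraph of section 12.1.4 reports that "about 10% of the enrolled children are tested positive by PCR".

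No power or precision is given for a comparison among positive children only.

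**The concern.** The power statement counts everyone enrolled, while the test counts only children in whom the organism was found or who were diagnosed with it. Question 1 serves the first objective and the first main study parameter (section 7.1), and section 4.4 gives its only power statement. If roughly nine in ten children drop out of the comparison, the claimed sensitivity to a small difference goes with them. A reader who relies on section 4.4 could take a non-significant result as evidence against even a small difference in load, when moderate differences would often be missed. The ROC threshold rests on the same children, so its precision is limited in the same way.

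**Working it through.** **Inputs.** Group size 500 and 500, alpha 0.05, power at least 90%, effect size d = 0.20 (section 4.4). Sidedness is not stated; two-sided is used below and one-sided is shown where it matters. Analysis sets and test: section 9, Question 1. Positivity: about 10% (sections 4.4, 9 and 12.1.4).

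**Step 1. Reproduce the stated figure.** For n per group, power ≈ Φ(d·√(n/2) − z), with z = 1.960 two-sided or 1.645 one-sided. At n = 500, 0.20 × √250 = 3.162. Power is Φ(1.202) = 88.5% two-sided and Φ(1.517) = 93.5% one-sided. The statement in section 4.4 reproduces for 500 versus 500.

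**Step 2. Size of the Question 1 sets.** 10% of 500 is 50 per group. This count is an assumption derived from the protocol's rates; the protocol does not state it. The range used is 25 per group (5%) to 100 per group (20%).

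**Step 3. Power at d = 0.20 in those sets (two-sided).** At n = 50, 0.20 × √25 = 1.00, and Φ(1.00 − 1.96) plus the negligible opposite tail is 17%.

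| Positives per group | d·√(n/2) | Power at 0.20 |
|---|---|---|
| 25 | 0.71 | 11% |
| 50 | 1.00 | 17% |
| 100 | 1.41 | 29% |

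The Mann-Whitney test gives about 16% at 50 per group. A one-sided test gives 26%.

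**Step 4. Difference detectable among positives.** For the t-test, d ≈ (1.960 + 1.282)·√(2/n). At n = 50 this is 3.242 × 0.20 = 0.648, or 0.655 with the t distribution. For Mann-Whitney under normality, divide the t-based value by √(3/π) = 0.977.

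| Positives per group | t-test, 90% power | Mann-Whitney, 90% power |
|---|---|---|
| 25 | 0.94 | 0.96 |
| 50 | 0.655 | 0.67 |
| 100 | 0.46 | 0.47 |

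For 80% power at 50 per group, the t-test value is 0.566, and 0.566 / 0.977 = 0.58 for Mann-Whitney.

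**Step 5. ROC precision (Hanley-McNeil).** Take AUC = 0.7, with a = 0.7/1.3 = 0.538 and b = 2 × 0.49/1.7 = 0.576. At n = 50 per group, SE² = [0.7 × 0.3 + 49 × (0.538 − 0.49) + 49 × (0.576 − 0.49)] / 2500, evaluated with unrounded a and b. This gives SE = 0.052 and a 95% interval of about ±0.10. The half-width is about ±0.15 at 25 per group and ±0.07 at 100.

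**Step 6. Unequal sets.** Serology could enlarge the group A set alone. With 50 in group B, power at 0.20 is 21% with 100 in group A, 24% with 200, and 27% even with all 500.

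**The case against.** Several points on the other side are fair.

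- **The counts are not fixed by the protocol.** Group B enters Question 1 through conventional PCR or culture, while the expected carriage of more than 10% refers to quantitative PCR and is a lower bound. Group A may also qualify by serology, which a PCR positivity rate does not cover. This stands, which is why the counts are given as an assumption with a range. The conclusion does not depend on them: power at 0.20 stays below 30% at 100 per group.
- **Group A might be thought to have a known upper limit.** A reader might add the 12% in section 4.4 to the 10% and infer at most 22 infections among the 100 older children, hence 62 cases in all. The document does not support that. The 12% is a detectable difference, and no infection rate is stated for group A children of 5 years and older.
- **The arithmetic in section 4.4 might be thought wrong.** A reader who assumes a two-sided test gets 88.5%, slightly under the stated 90%. Sidedness is not given, and a one-sided test gives 93.5%. No error can be claimed there.
- **The sentence may have meant all enrolled children.** Section 9 lists no such comparison of load. With about 90% of results negative, a rank test over everyone would hardly register load. In a simulation of 500 versus 500 with 10% positive in each group, a shift of 1.5 SD among positives gave power of only about 5 to 6%.
- **The study is called explorative, and a shift of 0.20 would be of little use for a diagnostic cut-off.** Both are true. They could justify making no power claim, but they do not make the existing one apply to Question 1.

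**Conclusion.** The point holds as a mismatch between the basis of the power statement and the set that is analysed. The claimed sensitivity to an effect size of 0.20 does not apply to Question 1. With about 50 positive children per group, power at 0.20 is about 17% and the difference detectable with 90% power is about 0.67, more than three times the stated figure. Over 25 to 100 positives per group, power runs from 11% to 29% and the detectable difference from 0.96 to 0.47.

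These figures assume two-sided testing at 0.05, equal numbers of positives, and approximate normality of load on a log scale.

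A reader might go further and infer that the first objective cannot be met. The protocol does not support that. The rationale for the ancillary study (section 12.1.1) reports that load seems higher in ill children, without a magnitude, and a large difference would be detectable with the planned numbers. Nor does the protocol say that a null result will be read as excluding a small difference; that is a risk created by the wording.

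**What to change.** In section 4.4, delete the claim that differences of 0.20 are demonstrable for the load comparison, and put in its place:

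> Assuming about 10% positivity (about 50 M. pneumoniae-positive children per group), the two-sided Mann-Whitney comparison has 90% power for a standardised difference of about 0.67 and 80% for about 0.58, assuming approximate normality of load on a log scale. With 25 to 100 positives per group, the 90% figure ranges from about 0.96 to 0.47. An AUC of 0.7 would be estimated to about ±0.10 (±0.15 to ±0.07).

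The cost is a change of protocol wording and a less favourable stated detectable difference. Enrolment, sampling, the Mann-Whitney test and the ROC analysis do not change.

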# TREATMENT OF SUBJECTS

This entire section is not applicable

## Investigational product/treatment

Use of co-intervention

## Escape medication

# INVESTIGATIONAL MEDICINAL PRODUCT

This entire section is not applicable.

## Name and description of investigational medicinal product

## Summary of findings from non-clinical studies

## Summary of findings from clinical studies

## Summary of known and potential risks and benefits

## Description and justification of route of administration and dosage

## Dosages, dosage modifications and method of administration

## Preparation and labelling of Investigational Medicinal Product

## Drug accountability

# METHODS

## Study parameters/endpoints

*Main study parameter/endpoint*

- Differentiation between asymptomatic colonization and infection by M. pneumoniae by using quantitative real time PCR.
- Age distribution of M. pneumoniae.
- Relation of genotype, co-infections or co-colonization and virulence of M. pneumoniae.

### *Secondary study parameters/endpoints*

Not applicable

### *Other study parameters*

Not applicable

## Randomisation, blinding and treatment allocation

Not applicable.

## Study procedures

Visit 1:

From each patient the following samples will be obtained

- Oropharyngeal swab
- Nasopharyngeal swab
- Nasopharyngeal lavage
- Serum (blood sample of 200 microliters)

Patients from group A will have their samples taken during their visit at the Emergency Department/HAP. In those cases many of the samples are taken for diagnostic reasons anyway. Samples can usually be split for clinical (diagnostic) and research purposes. This will minimize the burden for the patients.

Patients from group B are at the day care ward for surgical treatment. The blood sample will be drawn from the vena puncture, which is conducted by the anaesthesiologist, in order to obtain iv-access for administration of anaesthetics drugs. The other samples are taken after the patient has had their anaesthetics.

Patients from both groups fill out a short questionnaire about their health (history, use of antibiotics, smoking, attendance of day care centre, etc)

Visit 2:

Group A will be asked to return for a follow-up visit, 3 tot 4 weeks after their initial visit. During this visit another blood sample will be taken and there will be another short questionnaire.

Group B will not have to return to hospital. They will be phoned by a member of the research team to check if there were any respiratory tract infections in our healthy control or his/her family since the day of surgery.

Withdrawal of individual subjects

Subjects can leave the study at any time for any reason if they wish to do so without any consequences. The investigator can decide to withdraw a subject from the study for urgent medical reasons.

### *Specific criteria for withdrawal*

## Not applicable

## Replacement of individual subjects after withdrawal

## Not applicable

## Follow-up of subjects withdrawn from treatment

## Not applicable

## Premature termination of the study

Not applicable

# SAFETY REPORTING

## Section 10 WMO event

In accordance to section 10, subsection 1, of the WMO, the investigator will inform the subjects and the reviewing accredited METC if anything occurs, on the basis of which it appears that the disadvantages of participation may be significantly greater than was foreseen in the research proposal. The study will be suspended pending further review by the accredited METC, except insofar as suspension would jeopardise the subjects’ health. The investigator will take care that all subjects are kept informed.

## Adverse and serious adverse events

Not applicable

### Suspected unexpected serious adverse reactions (SUSAR)

Not applicable

### Annual safety report

Not applicable

## Follow-up of adverse events

Not applicable

## Data Safety Monitoring Board (DSMB)

Not applicable

# STATISTICAL ANALYSIS

Research questions and analysis

Question 1 (objective 1): does asymptomatic carrier state with M. pneumoniae exist (see question 3, we expect to find > 10%, using quantitative PCR) (10), and if so, can asymptomatic carrier state be differentiated from infection using quantitative PCR?

Analysis: in children with respiratory tract infections caused by M. pneumoniae (as defined by positive standard PCR, positive serology, and or positive culture, group A), results from the quantitative PCR (results in copies/ml) will be compared with the results from the quantitative PCR in asymptomatic children (healthy asymptomatic children with positive results from either standard conventional PCR or culture, group B) using the Mann-Whitney U test. A PCR value, which can differentiate asymptomatic carrier state from infection (threshold), will be determined using Receiver Operating Characteristic (ROC) curves. This value should have a high sensitivity and acceptable specificity.

Question 2 (objective 1): what is the sensitivity and specificity of this quantitative PCR?

Analysis: sensitivity and specificity will be determined using Receiver Operating Characteristic (ROC) curves. In addition we will investigate the sensitivity and specificity according to whether the quantitative PCR results in a positive or negative result (lowest possible detecting range is 10 copies).

Question 3 (objective 1): what is the prevalence of asymptomatic carrier state?

Analysis: prevalence of asymptomatic carrier state (a positive result with quantitative PCR) will be calculated in group A (children with a positive quantitative PCR result and RTI not caused by M. pneumoniae) and B (healthy asymptomatic children with a positive PCR result). We expect to find >10% in group B (10).

Question 4 (objective 2): does M. pneumoniae infection occur more often in children older than 5 years?

Analysis: children in group A with a RTI caused by M. pneumoniae will be divided in two groups, according to age (< 5 years and ≥ 5 years) and compared to each other, with respect to the prevalence using 2-test.

Below five years of age there’s a high prevalence of viral infections. It is therefore necessary to use a greater number of children with RTI in that group to find a reasonable number of M. pneumoniae infections. Using a pre-calculated number of children < 5 years (400) and > 5 years (100), the detectable difference will be 12 % assuming prevalence up to 10% in the < 5 years of age group.

Question 5 (objective 2): do children with M. pneumoniae and a viral or bacterial co-infection have more severe illness?

Analysis: children in group A with a RTI caused by M. pneumoniae will be divided in two groups: children without co-infection, and children with a viral or bacterial co-infection. Severity of disease will be scored according to diagnosis, severity of respiratory distress (days of required oxygen or mechanical ventilation and days of hospitalization. Groups will be compared using Mann-Whitney U test.

Question 6 (objective 3): does genotype of M. pneumoniae influence the rate of asymptomatic carrier state (level of PCR in healthy children, group B), and/or severity of disease?

Analysis: depending on the number of different genotypes of M. pneumoniae found, we will compare these different genotypes to PCR levels using Kruskal-Wallis test. This will be done in the asymptomatic children (healthy M. pneumoniae carrierstate) as well as the children with a M. pneumoniae RTI. Severity of disease will be scored according to severity of respiratory distress (days of required oxygen or mechanical ventilation) and days of hospitalization. This will be compared with different genotype by Kruskal-Wallis test in the symptomatic group (children with M. pneumoniae RTI).

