More recently, polymerase chain reaction (PCR) demonstrated the potential to produce rapid, sensitive and specific results, and is now considered the method of choice for direct pathogen detection. (8) However, there is justified concern when the PCR assay is used as the sole means of detection without culture, serology, or clinical data, because surveillance studies using culture and/or PCR indicate that a prolonged asymptomatic carrier state may occur in some persons. (9-12) Since it is not known whether there is a specific threshold quantity of M. pneumoniae in respiratory tract tissues that can differentiate asymptomatic carrier state from infection, a positive result by PCR may overestimate the clinical importance, and may result in unnecessary use of antibiotics. On the other hand, if quantitative PCR will demonstrate to be a reliable technique for diagnosing M. pneumoniae infection, M. pneumoniae will be diagnosed more often. This will result in more adequate treatment of RTI’s in children. It has been suggested that children colonized with M. pneumoniae might be an unrecognized reservoir for the spread of this pathogen. (12) The application of quantitative PCR assays will be crucial in optimizing diagnosing RTI by M. pneumoniae, and in gaining a better understanding of the carrier state associated with M. pneumoniae. Therefore, this is one of the main objectives of our study.

1. M. pneumoniae is thought to be a pathogen that causes pneumonia in children aged 5 years and older. Choice of treatment is based on this supposed age-distribution. Since M. pneumoniae is not susceptible to β-lactam antibiotics, a macrolide antibiotic is the first choice treatment in this age-group. In children younger than 5 years, β-lactam antibiotics are the first choice treatment, because M. pneumoniae is presumed to be a rare cause of RTI in this age-group. However, data on age distribution are conflicting. (13) Specialized diagnostic techniques showed that M pneumoniae might have a more important role in causing both upper and lower respiratory tract infections than previously thought; they seem to be frequent also in children aged less than 5 years. (4, 14) To address this issue, we will investigate the rate of infection among children belonging to different age groups.

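### Question 1 compares bacterial load among positives without regard to age; the 400/100 quotas do not guarantee age balance there, so part of any age effect on load could be read as an infection effect

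*Protocol*

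**What the plan says.** Section 9, Question 1 restricts the comparison to children with an M. pneumoniae RTI in group A (standard PCR, serology and/or culture positive) and asymptomatic children in group B who are positive by conventional PCR or culture. Their loads are compared "using the Mann-Whitney U test. A PCR value, which can differentiate asymptomatic carrier state from infection (threshold), will be determined" with ROC curves. No age term, age stratum or age-specific threshold is mentioned.

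Age is nevertheless the one factor on which enrolment is controlled. Section 4.1 sets group A at 500 children, "from which: 400 children <5 years and 100 children ≥ 5 years", and repeats this for group B: "Again: 400 children <5 years and 100 children ≥ 5 years". Section 4.4 treats infection as possibly age-dependent: "Assuming up to 10% M. pneumoniae infections below 5 years of age we will be able to detect a 12% difference" between the two bands. Question 4 tests that difference. Positivity in group B is given only overall: more than 10% in section 9 and about 10% in section 12.1.4, with no split by age. The Hypothesis in the Summary is that infection is as frequent under 5 as in older children. No section says that bacterial load depends on age.

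**The concern.** Equal quotas make A and B alike in age at enrolment. Question 1 does not analyse the enrolled children, however. It analyses those who turn out positive, and selecting on positivity keeps the age balance only if positivity varies with age in the same way in both groups. The protocol does not assume this. It leaves age dependence of infection open in Question 4 and is silent on age dependence of carriage.

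If the positives in A are older than those in B and load also depends on age, the plain rank test and the pooled ROC curve attribute part of the age difference to infection.

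A second point does not need any imbalance. If load depends on age, a single cut-off has different sensitivity and specificity below and above 5. The threshold is the main product of Aim I, and section 1 notes of current practice that "Choice of treatment is based on this supposed age-distribution", so readers will want to know how it performs in each band.

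**Working it through.** **Inputs from the protocol.** "For estimated group sizes in 2 years of 500 in group A and 500 in group B"; "effect-size (difference of mean/standard deviation) is 0.20 or larger"; "α = 0.05, power ≥ 90"% (section 4.4). Quotas 400 and 100 in each group (section 4.1). Infection in A 10% under 5, and 10% + 12% = 22% at 5 or over as the detectable alternative (sections 4.4 and 9). Positivity in B about 10% overall (section 12.1.4).

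**Inputs assumed.** Carriage in B of 10% in both age bands. An age effect d on log load, in SD units, from 0 upwards. Normal, fully observed log loads.

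**1. The plan's own figures.** Load, 500 against 500: 0.20/√(2/500) = 3.162, so two-sided power is Φ(3.162 − 1.960) = 88.5% and one-sided power Φ(3.162 − 1.645) = 93.5%. The two-sided value is within 2 points of the stated 90%. Infection by age, 400 against 100: the pooled rate is 62/500 = 0.124, the null SE √(0.124 × 0.876 × (1/400 + 1/100)) = 0.0368, and the alternative SE √(0.09/400 + 0.1716/100) = 0.0441. Power is Φ((0.12 − 1.96 × 0.0368)/0.0441) = 86%, so a 12-point difference is a reasonable detectable alternative.

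**2. Age among the positives.** A: 400 × 0.10 = 40 and 100 × 0.22 = 22. B: 400 × 0.10 = 40 and 100 × 0.10 = 10. The share aged 5 or over is 22/62 = 35.5% in A and 10/50 = 20.0% in B, a difference of 0.155.

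**3. How much of an age effect leaks through.** With no infection effect, the spurious mean shift is 0.155 × d, about one sixth of d. The spurious AUC is 0.5 + 0.155 × (Φ(d/√2) − 0.5).

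**4. Error rate.** Simulation with 62 against 50 positives split as in step 2, no infection effect, 5,000 runs per setting, nominal level 5%:

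| Age effect d (SD) | Shift (SD) | AUC | Mann-Whitney rejects | van Elteren rejects |
|---|---|---|---|---|
| 0 | 0 | 0.50 | 4.7% | 4.7% |
| 0.5 | 0.08 | 0.52 | 5.8% | 4.5% |
| 1.0 | 0.15 | 0.54 | 9.0% | 5.3% |
| 1.5 | 0.23 | 0.55 | 12.3% | 4.9% |

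Repeat runs gave 6 to 7%, about 9% and about 12% for the last three Mann-Whitney entries. Even at 2 SD the AUC reaches only 0.57, with 15% rejections.

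**5. Dependence on the assumed carriage pattern.** If A and B share the same pattern (10%/10% in both, or 10%/22% in both), the AUC stays at 0.50 and the Mann-Whitney test does not exceed 5%. It becomes conservative as d grows. If carriage were instead 15% under 5 and 5% at 5 or over, a 1 SD age effect would give 27% rejections and an AUC of 0.57. The protocol supports neither pattern over the other.

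**6. One cut-off, two bands.** Measure load from the mean of younger carriers, and let g be the infection effect. At cut-off c, specificity is Φ(c) under 5 and Φ(c − d) at 5 or over. Sensitivity is 1 − Φ(c − g) and 1 − Φ(c − g − d). These differ between bands whenever d is not 0, whatever the age mix.

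**The case against.** A reader might infer that selecting on positivity does unbalance age, and that the load comparison and threshold are therefore invalid. The documents do not support that. The Hypothesis in the Summary is equal infection frequency in the two bands, and with carriage also flat by age there is no imbalance. The 22% is what the design could detect, not what it expects, and the 10% is stated as an upper figure. Flat carriage by age is this review's assumption. No section gives an age effect on load, and at zero the unadjusted test is valid. Even with every assumption granted, a spurious AUC of 0.52 to 0.55 could not by itself produce a threshold with the high sensitivity the protocol wants. All of this stands, and it limits the point to a possible, modest bias.

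The simulation is also idealised. Group A may include serology-only cases with no detectable load, and the assay has a detection limit of 10 copies, so the error rates are illustrative. The remark on treatment in section 1 concerns how common infection is by age, not load or cut-offs; it shows why age matters to users, not that load varies.

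Finally, the study calls itself explorative, and an SAP that is not shown could add stratification. That is possible, but the protocol names the unstratified test for its first research question. Choosing the stratified version is a specific improvement to a stated method, not a request for missing detail.

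**Conclusion.** The point holds in conditional form, as a worthwhile improvement rather than an error that invalidates Question 1. The quotas protect the enrolled groups against age imbalance but not the positives that Question 1 compares. Bias needs two things together: positivity depending on age differently in A and B, and load depending on age. Under the detectable infection difference with flat 10% carriage, the positives would be 35% against 20% aged 5 or over. An assumed age effect of 0 to 1.5 SD would then give a false-positive rate of about 5% to 12% and a null AUC of 0.50 to 0.55. If either condition fails, there is no bias. Separately, if load depends on age, the single threshold will perform differently in the two bands even when age is balanced. The protocol leaves the age dependence of infection open and says nothing on the rest, so the safeguard is justified.

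**What to change.** In section 9, Question 1, replace the plain Mann-Whitney test by its age-stratified version (van Elteren), with the enrolment bands of section 4.1 (under 5; 5 or over) as strata. Report an age-adjusted AUC alongside the ROC curve. Show the sensitivity and specificity of the chosen threshold in each band, with confidence intervals, as descriptive results.

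The change is to analysis wording only, since age is already recorded and is the enrolment stratum. If age has no effect on load, it costs about 1 to 2 points of power: in simulation at a 0.5 SD infection effect, 72.5% against 71.4%, and 72.1% against 70.5% on a rerun. Estimates in the older band will be imprecise because they rest on about 10 to 22 positives per group; a specificity of 8/10, for example, has an exact 95% interval of about 44% to 97%. Two strata also leave age differences within each band uncontrolled, including within the under-5 band that makes up 80% of enrolment.
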